### Development of the intervention

The intervention is designed and developed based on theoretical evidence, input from key stakeholders and the target population and follows the guidelines from the Medical Research Council for the development and evaluation of complex interventions. [34]. A review from the literature and a systematic review from Papadopoulos et al. [19] identified the psychosocial variables which mediate the relationship between stigma and mental health for family carers of autistic children. Identification of modifiable psycho-social variables has led to the development of a theoretical framework with key variables to be targeted in the intervention. This is illustrated in Additional file 2: Figure S2.

To encourage input from the autism community, an online survey was carried out among the autism community (*n* = 112) about their views and suggestions to make an intervention more successful. Thematic analysis of the responses revealed that respondents suggested that parents’ self-esteem should be boosted, and that they would benefit from ‘ready-made’ phrases or information available to react to instances of stigma from the public, other family members and professionals. Respondents also showed a real desire to connect with other carers and to be able to share experiences and feelings. They explained however that childcare would be a barrier to attendance which is why a blend of online and face to face sessions has been chosen as the optimal mode of delivery.

### Content

The focus of the content will be on autism stigma and how to cope with this. A respectful and supportive environment will be encouraged where parents/carers can share their experiences and support and learn from each other. A description of the content of the sessions is shown in Table 1.

**Table 1 Tab1:** A brief overview of SOLACE

Number	Topic	Theme	Aim
1	Introduction	Exploration of autism and autism stigma. Autism myths and stereotypes will be challenged through psychoeducation and a group discussion about common stereotypes.	To make introductions and provide an overview of the sessions. To increase knowledge about autism. To reduce feelings of self-blame and increase self-esteem.
2	Coping with autism stigma	Group discussions of experiences of stigma using quotes from other parents. “How would you treat a friend” exercise.	To develop skills how to recognise and cope with stigma and to prevent internalising stigma.
3	Positive meaning of caregiving	Video clips of parents of autistic children showing how having an autistic child has changed them. Group discussion based on that. Free sharing time.	To increase the positive meaning associated with the caregiving role and increase self-compassion.
4	Resilience & self-esteem	Group task to work together to find “key phrases and responses” to stigmatising situations.	To increase resilience and increase self-esteem. To reduce social isolation and increase feeling of belonging.
5	Social support	Stress the importance of social support and discuss together how social support could be utilised and or improved.	To stress the importance of social support to help reduce social isolation.
6	Compassion & acceptance	Discuss the importance of self-care and self-compassion as well as acceptance of the child. Use video clips of how other parents have achieved this.	To increase feelings of self-compassion and acceptance.
7	Coping with autism stigma part 2.	Discuss the automatic thought cycle (self-fulfilling prophecy). Group discussion on how we can break this cycle.	To further develop skills how to recognise and cope with stigma and prevent internalisation of stigma
8	Next steps	Group discussions on how to disclose the diagnosis to others and to provide list of support for future.	To further increase self-esteem and reduce social isolation To conclude the sessions and provide “next steps” for future reference
9	Focus group	Group discussion evaluating SOLACE	To evaluate the acceptability and practicality of SOLACE and the outcome measures.

### Format

Three of the intervention sessions will be face to face (session, 1, 4 and 8) and the remaining sessions will be delivered via videoconference to overcome potential barriers that parents and carers are likely to experience such as time commitment, travel and childcare issues. It has been decided that eight sessions should offer the right balance between time commitment and being beneficial.

### Control group

Participants allocated to the control group will be asked to continue with their normal day to day life as usual. Measures will be taken again post-intervention period (week 8) and 6 weeks post intervention (week 14) to describe potential preliminary differences between the control and intervention group. After the study period, an information pack including useful information and activities that were part of SOLACE will be provided to this group.

### Outcome measures

Continuation criteria will be used to assess if further evaluation of this intervention is justified, through a formal RCT. The criteria for continuation will be based around feasibility and acceptability. A mix of quantitative and qualitative evaluation processes will be used to evaluate the feasibility of the intervention.

The outcome measures to assess feasibility and acceptability are the following:Recruitment rate, including willingness to be randomised.Drop-out rates including reasons will be recorded to help determine the acceptability of the intervention to participants.Missing data will be descriptively analysed in order to evaluate the acceptability of the data collection measures and procedures.Incidence of adverse events will be recorded that may arise during the intervention period.To evaluate the acceptability of SOLACE and the outcome measures, participants from the intervention group will be invited for a qualitative focus group discussion in week 9. The focus group interview will be audio-recorded for analysis. A topic list will be used to evaluate the intervention content, structure, format and mode of delivery. Positive quality feedback of participants regarding their experience of undertaking SOLACE should indicate whether a larger trial may be feasible.

### Primary outcome measure

#### Psychological well-being

Psychological well-being will be measured with the validated and reliable 5-item ‘Mental Health Inventory’(MHI-5) [35] . Participants are asked to rate on a six-point scale how often they felt as described during the past month, e.g. ‘During the past month, how much of the time were you a happy person’. The MHI-5, which is used as the measure of common mental disorder, has excellent validity and reliability in measuring symptoms consistent with depression and anxiety [36] and has a long history of use in large-scale health studies [37], including within the caregiver population [36].

#### Secondary outcome measures

Public stigma will be measured using the Perceived Public Stigma Scale [38]. This scale contains eight items on a six-point Likert scale ranging from 0 (strongly disagree) to 5 (strongly agree) with higher scores indicating higher levels of perceived public stigma. A sample statement is ‘Most people think less of an autistic person than they do of other people’. This scale has been used with carers and parents of autistic children and shown good reliability (*α* = 0.83) [38].

#### Courtesy stigma

The Perceived Courtesy Stigma Scale (PCSS) [38] contains seven items adapted from the Devaluation of Consumer Families Scale [39]. Caregivers rate each item on a four-point Likert scale ranging from 0 (strongly disagree) to 3 (strongly agree) with higher scores suggesting higher levels of perceived courtesy stigma. The PCSS has been used with parents of autistic children and its validity was demonstrated by its significant correlations with theoretically related constructs [38] and a good reliability score of *α* = 0.89 [38]. Items include statements like ‘most people blame parents for their child being autistic’.

#### Affiliate stigma

Affiliate stigma is measured with the Affiliate Stigma Scale [25]. This 22-item scale has been adapted by the study team to be suitable for UK caregivers. Three items with the lowest factor loadings have been dropped in order to decrease the number of negatively worded items based on work by Werner and Shulman [28]. Each item is rated on a 4-point Likert scale (1, strongly disagree to 4 strongly agree).

#### Self-esteem

Rosenberg’s 10-item Self-Esteem Scale [40] is used to measure self-esteem. An overall index can be calculated by averaging the score on the 10 items scored on a 4-point Likert scale. The Rosenberg Self-Esteem Scale is a widely used measure of self-esteem which has been shown to have good internal consistency in various populations.

#### Self- compassion

Self-compassion is measured with the Self-Compassion Scale-Short Form [41], a modified version of the Self-Compassion Scale [42]. It measures six components of self-compassion: self-kindness, self-judgement, common humanity, isolation, mindfulness, and over-identification. The 12 items are rated on a 5-point response scale ranging from 1 (almost never) to 5 (almost always). The SCS-SF has demonstrated good internal consistency (*α* ≥ 0.86) and a near-perfect correlation with the long-form self-compassion scale (SCS) (*r* ≥ 0.97) [41].

#### Positive meaning of caregiving

Based on Werner and Shulman’s [28] study, positive meaning in caregiving will be measured with 11 items taken from two sources: from parents’ qualitative responses to the question ‘How has caregiving for your child affected your life?’ in a study by Meyers et al. [43] and from the Perceived Benefits scale constructed by Green [44] containing 5 items. A sample item is ‘Being a parent/carer to an autistic child with a taught me kindness, patience and happiness’.

#### Self-blame/responsibility

The Self-blame and Responsibility Scale has been translated from Chinese by Mak and Kwok [27] and has been slightly adapted to make it more suitable for the UK population and the wording has been changed to ‘autism-first language’ as is generally preferred by the autism community.

#### Social Support

To measure perceived social support, the Medical Outcomes Study: Social Support Survey [45] will be used. This scale measures four components of perceived availability of social support, including (1) emotional support/informational support, (2) tangible support (including material support), (3) positive social interaction (does person have friends that are available to have fun) and (4) affectionate support (including loving and nurturing relationships). It has shown good reliability (*α* = .85) and validity on total scale (*α* = .88) as well as subscales.

#### (Subjective) social isolation

The short-form UCLA Loneliness Scale [46] will be used to measure social isolation. The UCLA Loneliness Scale has been found to be a highly reliable measure—both in terms of internal consistency and test–retest reliability over a one-year period—and to have convergent and construct validity [46].

#### Other baseline measures

Information on general demographic variables such as age, gender, ethnicity, marital status, income, religious affirmation, educational level, child’s primary diagnosis, number of children, age of child, time since diagnosis and current use of support groups.

### Statistical analysis

Statistical analysis (using IBM SPSS v23 software) of the quantitative outcome measurements will be conducted following tool analytical guidance. Within group comparisons of the outcomes, measures will be made as well as between groups comparisons to examine preliminary effectiveness.

Kolmogorov–Smirnov tests will be initially conducted to establish the normality of the data. Depending on the normality of distribution, independent samples *T* tests, Mann–Whitney *U* tests and/or chi-square tests will be used to compare the outcome measures between the two groups. To assess potential within-group differences, dependent *T* tests (for normal distribution) or Wilcoxon signed-rank tests (for non-normal distribution) will be used. Individual and group-level descriptive analyses of both the frequency and/or central distribution (medians, means, standard deviation, range) of independent and dependent variables will also be conducted. Standard effect sizes of the primary outcome measure will be calculated (Cohen’s *α*) with confidence intervals to provide an initial estimate for sample size calculation for a future main RCT.

Furthermore, quantitative data will be descriptively analysed to assess rates and patterns of recruitment, follow-up and retention rates, and willingness of randomisation. The distribution of missing data within each measure will help to establish the acceptability of measures. Missing data will also be described via frequencies and cross tabulations against background characteristics to further assess the acceptability of the measurement tools.

Qualitative data will be thematically analysed using Nvivo (v11). This will involve in-depth familiarisation with the focus group data, systematic identification of codes to form a coding frame, indexing the data according to the coding frame to identify common themes and interpreting the findings in the context of other research [47].

The Consolidated Standard of Reporting Trials (CONSORT) extension to pilot trials will be followed for reporting the trial.

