**Methods:**

A pilot randomised controlled trial feasibility study will be implemented. A group receiving the SOLACE stigma support intervention (*n* = 12) will be compared against a control group not receiving any additional intervention (*n* = 12). Family carers of autistic children up to the age of 10, who have been recently diagnosed or are currently undergoing diagnosis, will be recruited for the study. Participants will be randomly allocated to the intervention or control group and will take part in eight weekly group-based sessions designed to improve the well-being of the parents primarily through increasing their resilience to stigma. Feasibility will be determined by recruitment and retention rates and a qualitative focus group evaluating the acceptability of the intervention and outcome measures. The primary outcome of interest is psychological well-being, and depending on the normality of distribution, independent samples *T* tests will be used to compare the outcome scores between the two groups and dependent samples *T* tests for differences within the group. Other outcomes of interest are stigma, self-stigma, self-esteem, self-blame, social isolation, self-compassion and perceived responsibility and control.

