## Methods

### Design

This study is a feasibility study of a parallel randomised controlled trial (RCT) that compares changes in outcomes of interest among parents/carers allocated to the SOLACE experimental group against parents/carers allocated to a control group (no intervention). Standard Protocol Items: Recommendations for Interventional Trials (SPIRIT) checklist was used to structure and develop this protocol.

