### Sample size

As this is a feasibility study, it is not powered to determine statistical significance. The target recruitment for this feasibility trial is 24 (12 per group). This number is deemed appropriate for the study aims and consistent with recommendations for behavioural group intervention with this population [32].

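### Within-arm before/after significance tests are planned alongside the randomised comparison to examine preliminary effectiveness, and nothing marks them as descriptive only

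*Protocol article*

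**What the plan says.** The Design section describes a randomised parallel trial that "compares changes in outcomes of interest among parents/carers allocated to the SOLACE experimental group against parents/carers allocated to a control group". The contrast the design is built for is therefore change in one arm against change in the other.

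The Statistical analysis section sets out two sets of comparisons: "Within group comparisons of the outcomes, measures will be made as well as between groups comparisons to examine preliminary effectiveness". For the first set, dependent t tests apply if the data are normal; otherwise "Wilcoxon signed-rank tests (for non-normal distribution) will be used". For the second set, independent t tests, Mann–Whitney tests and/or chi-square "tests will be used to compare the outcome measures between the two groups". Descriptive summaries (means, medians, SDs, ranges) are a separate, additional item, so the within-group tests are not simply the descriptive part of the analysis.

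The abstract does the same for psychological well-being: independent t tests between the groups, and dependent "tests for differences within the group".

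The Statistical analysis section also plans a standardised effect size with confidence intervals for the primary outcome measure, as an input to the main trial's sample size. It does not say whether this is a between-arm or a within-arm effect.

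**The concern.** A paired test within the SOLACE arm asks whether that arm changed, not whether SOLACE changed it. The eligibility section takes carers whose child was diagnosed in the past 12 months or is still being assessed, and follow-up runs to week 14. Some shift in well-being, stigma or self-blame over that time is plausible without any intervention, and the control arm exists to remove it. A within-arm p-value leaves it in.

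Two things are at stake. First, a significant improvement in the SOLACE arm could be reported as a preliminary effect, particularly if the control arm happens to miss significance. Second, because the effect size for the main trial is not specified as between-arm, a within-arm figure could be carried into the sample-size calculation. If both arms had improved, that figure would include the background improvement and the main trial would be too small.

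**Working it through.** **Plan's own figure.** There is no power-based figure to reproduce. The Sample size section gives only a feasibility target ("The target recruitment for this feasibility trial is 24 (12 per group"), and 12 + 12 = 24 is consistent.

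**Inputs**
- n = 12 per arm (Sample size section).
- Within-arm test: paired t test (Statistical analysis section).
- Assumed, because the article gives neither: two-sided alpha 0.05, and a mean change d shared by both arms, in SDs of the change score, from 0 to 1.0.
- True SOLACE effect: zero, so d is the same in both arms.

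**Formulas**
- Under d, the paired t statistic is noncentral t with 11 df and noncentrality d√12. The critical value is t(0.975; 11) = 2.201.
- u = P(T > 2.201): significant improvement in the SOLACE arm.
- l = P(T < −2.201): significant worsening; p = u + l.
- P(SOLACE improves significantly, control not significant) = u(1 − p), since the arms are independent.

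**Worked case, d = 0.5.** Noncentrality = 0.5 × 3.464 = 1.732; u = 0.3526; l = 0.0002; u(1 − p) = 0.3526 × 0.6472 = 0.228.

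| d | u: SOLACE arm improves significantly | u(1 − p): and control not significant |
|---|---|---|
| 0 | 0.0250 | 0.0238 |
| 0.2 | 0.0925 | 0.0835 |
| 0.3 | 0.1564 | 0.1317 |
| 0.4 | 0.2440 | 0.1843 |
| 0.5 | 0.3526 | 0.2282 |
| 0.6 | 0.4747 | 0.2493 |
| 0.8 | 0.7137 | 0.2043 |
| 1.0 | 0.8829 | 0.1034 |

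The last column peaks at 0.25 near d = 0.62 and then falls, because the control arm also becomes significant. The middle column keeps rising.

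**With dropout.** With 10 analysed per arm and d = 0.5, the two figures are 29% and 21%.

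**Between-arm test on change.** The shared d cancels in the difference between arms, so the false-positive rate does not depend on it. Simulation (200,000 trials per setting) gave 5.0% to 5.1% at d = 0, 0.3, 0.5 and 0.8, and reproduced the within-arm figures.

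**Power of the valid test.** An independent t test on 12 per arm has about 22% power for a true difference of 0.5 SD. The randomised comparison may well be inconclusive while a within-arm test is significant.

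**The case against.** The strongest reply is that the valid contrast is planned and nothing decisive depends on the other one. The Design section defines the comparison between arms, the Control group section says the control measurements serve to describe differences between the groups, and the between-group tests are listed first. Continuation to a full trial rests on feasibility and acceptability (Outcome measures). The Sample size section says: "As this is a feasibility study, it is not powered to determine statistical significance". The Discussion allows only preliminary conclusions. This stands, and it limits the severity.

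The sentence on preliminary effectiveness can also be read so that the purpose attaches to the between-group comparisons alone. That is possible, but the within-group tests then have no purpose beyond detecting change within an arm, and still nothing ranks them below the randomised contrast.

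A reader might infer that the plan will declare an effect whenever one arm is significant and the other is not. The article contains no such rule; the 13% to 25% shows what would follow if results were read that way. Nor should one count every trial in which the arms disagree (27% to 50% over the same range of d, and 9.5% with no change): those figures include control-only results, and the 9.5% also includes significant worsening. Neither would be taken as a signal for SOLACE.

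The caveats about small numbers do not answer the point itself. Where there is shared improvement, a larger sample makes a significant within-arm result more likely, not less.

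**Conclusion.** The concern holds at moderate severity. The article states a choice to test change within each arm for significance next to the randomised comparison, without marking those tests as descriptive. Such tests cannot separate a SOLACE effect from change over time.

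The size depends on an assumed shared improvement and an assumed two-sided alpha of 0.05. With no true effect and 12 per arm, a shared improvement of 0.3 to 0.6 SD of change gives a significant SOLACE-arm improvement in about 16% to 47% of trials per scale, and in 13% to 25% with control not significant. At 0.2 SD these are 9% and 8%. With no shared change they are 2.5% and 2.4%, so there is no inflation without drift, and the article gives no figure for drift.

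A stronger reading, that this invalidates the trial's conclusions or must block it, is not supported: effectiveness is a secondary, unpowered objective and the between-arm comparison is already planned.

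**What to change.** In the Statistical analysis section, and to match in the abstract:
1. Report change from baseline by arm descriptively (means, SDs, plots), without p-values.
2. State that preliminary effect is judged only on the between-arm difference, in change or adjusted for baseline, with its confidence interval.
3. State that the standardised effect size carried to the main trial is the between-arm one.

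The cost is a few sentences and less analysis; no new data are needed. The downside is that no within-arm p-values can be quoted. If the sponsor prefers to keep the paired tests, a sentence labelling them descriptive and not evidence of effect would remove most of the problem.

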### Ethical considerations

This study is being conducted in accordance with the ethical guidelines of the Institute of Health Research to ensure trial integrity as well as participants’ safety and well-being. Ethical approval was granted on January 1, 2018 (ref: IHREC812), from the University of Bedfordshire, Institute of Health Research’s ethics committee.

Respondents who are interested in taking part will receive detailed information about the study and have the opportunity to ask questions. Digital informed consent will be obtained from all participants before the start of the study. Participants are allowed to withdraw from the study at any time and it will be made clear that their anonymity will be respected at all times in the dissemination of results.

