## Discussion

The study described here aims to determine the feasibility and preliminary impact of an 8-week psycho-social stigma support intervention, ‘SOLACE’, with a group of parents and carers of newly diagnosed autistic children. To our knowledge, this study will be the first RCT to evaluate the feasibility and preliminary effects of a stigma support intervention for parents/carers of autistic children. As previously highlighted, parents/carers of autistic children are particularly vulnerable to poor mental health and well-being, and the stigma of autism likely significantly contributes to this. Therefore, an intervention that is evidenced to improve psychological well-being in part through increasing resistance to stigma will be of substantial benefit to families and, ultimately, their children. This study represents the first step towards achieving this goal. The learning generated from this study will enable the preparation for a future larger trial that can more confidently assess SOLACE’s effectiveness in improving psychological well-being.

The strength of the study design is the inclusion of a qualitative analysis to assess the feasibility of the intervention. Further, this feasibility study will provide a reliable indication of the sample size needed for an RCT testing the effectiveness of the intervention. It will also address a large gap in the autism-stigma literature since not much is known yet about the path between stigma and psychological well-being. However, as usual with feasibility studies, only preliminary conclusions on the effectiveness of the intervention can be drawn, owing to the small sample size.

The carer population is known to experience many barriers to attendance. SOLACE aims to overcome this barrier by delivering a combination of face to face and online sessions. This should also mean it is relatively easy to implement and to replicate in the future. If SOLACE is feasible and eventually proven to be effective, then health and social care services can commission and include the intervention as part of their service provision. The evidence may also be used to help shape future local and national (and potentially international) autism policy so that the importance of stigma in relation to caregivers’ psychological well-being and their caregiving role is emphasised.

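### The MHI-5 effect size rests on t or Mann–Whitney tests that use only scores observed at each time point, so loss that is related to well-being and unequal between arms would bias it in either direction

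*Protocol article*

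**What the plan says.** All of this is in the protocol article; no separate analysis plan is at hand.

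- **Tests.** Under Statistical analysis, "independent samples *T* tests, Mann–Whitney *U* tests and/or chi-square tests will be used to compare the outcome measures between the two groups", depending on normality. Within arms the choice is a dependent t test or a Wilcoxon signed-rank test. No baseline-adjusted or repeated-measures model is named.
- **Time points.** Scores are taken at baseline, week 8 and week 14 (Randomisation and blinding; Control group).
- **Missing scores.** Outcome measures and Statistical analysis both treat them as evidence on acceptability: "Missing data will also be described via frequencies and cross tabulations against background characteristics to further assess the acceptability of the measurement tools". Neither section links them to the effect estimate.
- **Loss.** Under Ethical considerations, "Participants are allowed to withdraw from the study at any time". Harms ties that option to distress. The section Intervention: SOLACE gives the retention aids (a private Facebook group and weekly reminders) to the experimental arm only.
- **Use of the estimate.** Statistical analysis plans an MHI-5 effect size with a confidence interval as a first input to the main trial's sample size. The Discussion describes the resulting indication of sample size as reliable.
- **Status.** Under Sample size, "As this is a feasibility study, it is not powered to determine statistical significance". The target is 24 carers, 12 per group.

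**The concern.** A two-sample test needs a score at the time point tested, and a paired test needs both scores of the pair. Applied as named, the tests discard the earlier scores of a carer who later stops responding. The between-arm test also leaves the baseline score unused even when nobody is lost. If missingness differs between week 8 and week 14, the two contrasts rest on different sets of carers.

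This matters if loss is related to well-being and unequal between arms, and the article makes both plausible. MHI-5 measures symptoms of depression and anxiety, and distress is a stated reason for leaving. Only one arm gets retention aids, which points to more loss in control. Only that same arm carries eight sessions, which points the other way. The direction therefore cannot be predicted. The planned confidence interval shows sampling error, but nothing in the planned analysis would show a shift caused by selective loss.

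**Working it through.** The article gives no power, SD, target difference or expected drop-out, so there is no planned figure to reproduce beyond 12 + 12 = 24. One carer is 1/12 = 8% of an arm, and three carers are 25%.

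**Assumptions (not in the article).** Scores have SD 1 and correlation 0.65 between any two time points. The true difference is 0.50 SD at weeks 8 and 14. Loss occurs after week 8 and removes the carers with the lowest value of x = week 8 score + independent noise of equal variance.

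**Shift in one arm's observed week 14 mean.**
- Correlation of the week 14 score with x: 0.65/√2 = 0.460.
- Mean of a standard normal after its lowest 25% is removed: φ(−0.674)/0.75 = 0.318/0.75 = 0.424.
- Shift: 0.460 × 0.424 = 0.195 SD upward in the arm that loses carers.

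**Observed week 14 difference (true value 0.50).**

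| Loss SOLACE / control | Difference |
|---|---|
| 10% / 0 | 0.59 |
| 17% / 0 | 0.64 |
| 25% / 0 | 0.50 + 0.195 ≈ 0.69 |
| 33% / 0 | 0.75 |
| 0 / 25% | 0.50 − 0.195 ≈ 0.31 |
| 25% / 25% | 0.50 |
| any, unrelated to scores | 0.50 |

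Large simulations agree with these values. In the SOLACE-only cases, using the observed baseline and week 8 scores returned 0.50 each time. Differences are in units of the SD among all randomised carers. Selected completers vary slightly less, so a d computed from them would be slightly larger.

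**Effect on a main-trial calculation** (80% power, two-sided 5%, both assumed): n per arm = 2(1.960 + 0.842)²/d² = 15.70/d².
- d = 0.50: 63
- d = 0.69: 33
- d = 0.31: 164

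**Sampling error at 12 per arm.** The 95% half-width for d = 0.50 is 1.96 × √(2/12 + 0.50²/48) = 1.96 × 0.415 = 0.81.

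**Gain from a common-baseline model.** With no loss, the SE of the simple difference is √(2/12) = 0.41. With baseline as a response and a common baseline mean it is about √[(2/12)(1 − 0.65²)] = 0.31, or about 0.32 in simulation. With three SOLACE losses as above, simulated root-mean-square error falls from about 0.47 to about 0.35.

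**Limit of the gain.** In a separate simulation, loss depended on the unobserved final score itself (correlation 0.6, loss 33% in SOLACE and 8% in control). Completers gave 0.70, and baseline adjustment reduced this only to 0.63, against a true 0.50.

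**The case against.** **The article never says completers only, and handling of missing scores is commonly left to an analysis plan.** This stands in part. A reader might infer a stated completers-only rule. There is none, and imputation before testing is not excluded. The point is therefore not that a missing-data rule is absent. It is that the article itself names the tests, and these cannot use partial follow-up. The Design section speaks of comparing changes, but a test on change scores would equally drop anyone without the later score.

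**Selective loss need not bias the comparison.** This stands. A reader might infer that bias follows simply because carers who fare badly leave. It does not: with equal loss in both arms the difference stays at 0.50. With more loss in control, SOLACE looks worse than it is, and the one-sided retention aids make that at least as plausible as the reverse.

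**Missed sessions are not missed questionnaires.** This stands. The Discussion's remark on barriers to attendance might be read as forecasting missing MHI-5 scores. It concerns sessions, while outcomes are collected through an online survey platform.

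**Noise dominates, and the study is a feasibility study.** Sampling error does exceed every shift shown, effectiveness is a secondary objective, and only preliminary conclusions are claimed. This limits the importance of the point. It does not remove it, because the estimate has a stated use and the common-baseline model reduces error even when nobody is lost.

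**Conclusion.** The point holds in a conditional form. As named, the tests drop carers without a score at the time point tested and, between arms, make no use of baseline. If loss is both related to well-being and unequal between arms, the MHI-5 effect size is biased, and the sign depends on which arm loses more. Under the stated assumptions, 25% loss in one arm moves a true 0.50 to about 0.69 or about 0.31. Equal loss, or loss unrelated to scores, moves it by nothing. The size depends on the assumed correlation of 0.65, on the loss mechanism and on the drop-out rate, none of which the article gives. The shifts lie inside the sampling error of about ±0.8 SD. This is therefore a worthwhile improvement to a feasibility analysis and not a flaw that invalidates it. The documents do not support a claim that SOLACE will be favoured.

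**What to change.** Under Statistical analysis, for MHI-5 and for other scales that are approximately continuous:

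- Take the between-group estimate from a likelihood-based repeated-measures linear mixed model. Use baseline, week 8 and week 14 scores as responses, a common baseline mean, arm-by-time effects at weeks 8 and 14, and a simple covariance structure.
- Include every randomised carer in the assigned arm, whatever their session attendance.
- Report the week 8 and week 14 differences with confidence intervals, and base the effect size carried to the main trial on these.
- Keep the planned t or Mann–Whitney comparison as a sensitivity analysis, which also covers clearly skewed scales.

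**Cost.** Analysis wording only: no new data are needed, and the model can be fitted with the MIXED procedure in the SPSS version already named. It relies on approximately normal residuals and on scores missing at random, so it does not remove bias from loss that depends on unobserved scores. With 24 carers, a rich covariance structure should be avoided.
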